**Fig. 2 Fig2:**
[figure not shown]
The study design flowchart describing all the steps of the study

### Assignment of interventions: blinding

#### Who will be blinded {17a}

This will be a double-blinded study. Participants will be assigned to exercise plus AMPS or Exercise plus SHAM group. Thus, participants will be not aware if they are assigned to active AMPS or sham. Also, the researchers responsible for outcome assessments, data entry, and statistical analysis will be blinded to the group assignments. The leading research who will be in charge of the AMPS therapy will not be blinded, since it is not possible.

#### Procedure for unblinding if needed {17b}

In case a participant report to know their intervention group during the trial, it will be immediately communicated to the leading researcher and the participant will be excluded from the study. At the end of the study, in case the treatment is effective, it will be offered to these participants.

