#### Intervention description {11a}

##### Automated mechanical peripheral stimulation

AMPS therapy will be applied through a therapeutic device (Gondola, Ecker Technologies, Lugano, Switzerland), which will be fitted to each patient’s feet. The device consists of a foot stand for each foot with two electric motors that activate two 2-mm-diameter metal bars. The mechanical pressure stimulus occurs when the motors are activated. Before application, the device is adjusted so that the stimulus is applied to two specific areas for each foot, at the base of the first metatarsal joint and at the head of the hallux of the right and left feet. The intensity of the pressure is adjusted to reach the participant’s pain threshold (which normally occurs around 0. 3–0. 9 N mm^2^), defined as the moment when the participant reports that they began to feel pain (the moment of transition between the strong pressure and the painful pressure and the first time the visual analog scale (VAS) is greater than 0) or at the moment when the monosynaptic reflex appears in the anterior tibial muscle. After these preparatory procedures, treatment begins. The therapy will be carried out in 4 cycles. A cycle is completed when the four target areas are stimulated, which requires 24 s (6 s per area) so the complete therapy lasts 96 s [26].

The SHAM intervention will replicate the same procedure described for active AMPS. However, a rubber adapter will be positioned at the tip of the metal bars to increase the contact surface area and the pressure will be set to the sensorial threshold (i.e. when the patient report that they feel a touch at the point). AMPS sessions will be performed 24 h before all the exercise sessions [27].

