##### Physical exercise program

Physical exercise sessions will be composed of:
Warm-up (5 min): patients perform stretching of the main muscle groups of the upper limbs, lower limbs, and trunk.Aerobic exercise (30 min): Patients will perform continuous aerobic exercise consisting of walking on flat ground and ramps, with intensity between 40 and 60% of the heart rate reserve.Strengthening exercises (20 min): volunteers will perform resistance exercises (2 series × 15 repetitions) for the upper and lower limbs, and the trunk working the following muscle groups: shoulder flexors, extensors, and abductors; elbow flexors and extenders; trunk extensors and flexors; knee flexors and extenders; and dorsiflexes and plantar flexors.Cool down (5 min): Stretching of the main muscle groups worked during the sessions and relaxation.

After 6 weeks and in the end of the intervention program, the participants will be asked to inform which kind of intervention they thought they had been on (i.e., placebo or active) and to report their confidence level rating on a scale of 0–10, with 0 meaning “not at all confident” and 10 “extremely confident” that they received the active therapy [28].

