#### Plans to promote participant retention and complete follow-up {18b}

A weekly phone call will be made to participants in both groups, asking about their health status and reinforcing the pre-session recommendations for physical exercise. Moreover, the participants who wish and agree, will be added to a telephone messenger group app with the objective of solving doubts and share information and experiences about PD.

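### Participants who report knowing their allocation are excluded after randomisation; this may depend on arm and perceived benefit, and the planned intention-to-treat analysis cannot recover outcomes that were never collected

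*Protocol article*

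**What the plan says.** **The rule.** Section {17b}, on unblinding, deals with anyone who says, while the trial is running, that he or she knows the allocated group. The consequence is that "it will be immediately communicated to the leading researcher and the participant will be excluded from the study". The section adds that these participants will be offered the treatment at the end of the study if it proves effective. It does not mention continued assessment.

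**The stimuli.** Intervention description {11a} sets active AMPS at the participant's pain threshold. For sham, a rubber adapter is fitted and "the pressure will be set to the sensorial threshold".

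**The allocation question.** Under Physical exercise program: "After 6 weeks and in the end of the intervention program, the participants will be asked to inform which kind of intervention they thought" was theirs. Each must also "report their confidence level rating on a scale of 0–10" that it was the active therapy.

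**Contact between participants.** The retention section {18b} states: "A weekly phone call will be made to participants in both groups". A separate sentence says that those who opt in "will be added to a telephone messenger group app with the objective of solving doubts and share information and experiences about PD".

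**Assessments and analysis.** Outcomes {12} has two time points, baseline and after 12 weeks. The section on non-adherence and missing data {20c} promises per-protocol and intention-to-treat analyses with multiple imputation. It defines per-protocol by 70% attendance and completion of both evaluations. Unblinding is not a criterion there.

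**The concern.** Randomisation protects the comparison only if what happens afterwards does not select participants differently in the two arms. Here the trigger for removal is a participant's stated belief about allocation. That belief can be fed by the sensation of the stimulus, which differs by arm by design, and by whether the participant feels better. If either matters, those who stay in the two arms are no longer comparable.

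One of the three primary outcomes, the PDQ-39, is self-reported and so is especially exposed to a link with perceived benefit.

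Two other features raise the risk. The week-6 allocation question invites statements about allocation in mid-treatment, and no wording separates a confident answer from a report of knowing. The messenger group invites participants to exchange experiences, and nothing says it is separated by arm.

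**Working it through.** **1. The rule against the analysis sets.** A participant who reports knowing the group at, say, week 6 leaves before the only post-baseline assessment.
- Per-protocol set: lost, because the final evaluation is missing, although unblinding itself is not a criterion.
- Intention-to-treat set: can be retained only through imputation. With two time points there is no intermediate outcome, so the model has little beyond arm and baseline to work with. It would largely reproduce the comparison among those who stayed, including any selection in it.

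**2. The plan's own figure.** The point rests on no stated figure, but the sample size gives the scale. Sample size {14} gives 19 per group for an effect size of 0.80 and enrols 25, an allowance of 25 − 19 = 6 per group (6/25 = 24%). By the normal approximation, n = 2(z_α + z_β)²/d²:
- one-sided: 2(1.645 + 0.842)²/0.64 = 19.3, so 20;
- two-sided: 2(1.960 + 0.842)²/0.64 = 24.5, so 25.

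The stated 19 is therefore close only to a one-sided calculation. Sidedness is not stated. That is a separate matter and does not affect this point.

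**3. Possible bias with no true effect.** The documents give no rate of reported knowledge and no correlation, so these are assumptions: a fraction r of one arm is excluded, namely those at one extreme of perceived benefit; perceived benefit has correlation ρ with the outcome; the outcome SD is 1. The mean of those remaining in that arm shifts by

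ρ · φ(z₁₋ᵣ)/(1 − r).

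For r = 0.20, z = 0.842 and φ(z) = 0.280, so φ/(1 − r) = 0.280/0.80 = 0.350.

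| r in one arm, 0 in the other | ρ = 0.3 | ρ = 0.5 |
|---|---|---|
| 10% | 0.058 SD | 0.097 SD |
| 20% | 0.105 SD | 0.175 SD |
| 30% | 0.149 SD | 0.248 SD |

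At 20%, 20 against 25 remain, with standard error √(1/20 + 1/25) = 0.30 SD. The two-sided type I error rises from 5% to 6.4% (ρ = 0.3) or 9.0% (ρ = 0.5). With 10% excluded in each arm by the same mechanism, the bias is zero.

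**4. Direction.**
- Active participants who feel most benefit conclude that they are on active and leave: the shift is against AMPS.
- Active participants who feel least benefit conclude that they are on sham and leave: a shift of the same size in favour of AMPS, by symmetry.
- Sham participants who feel no benefit leave: the comparator improves, and the shift is against AMPS.

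**5. Loss of numbers.** Excluding 20% of an arm uses 0.20 × 25 = 5 of the 6 places allowed. The same 6 must also cover the exclusions in {11b} and {11d}. A t-test at d = 0.80 with 25 per group has 79.1% power two-sided (87.4% one-sided). With an assumed 30% excluded from the active arm and 10% from sham, power falls to 68.7% (79.4%).

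**The case against.** Several stronger readings are tempting, and the documents do not support them.

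- **That a confident week-6 answer itself leads to exclusion.** The question asks for a belief, and the rule acts on a report of knowing. Nothing links the two. The 0–10 scale measures confidence of having received active therapy, not certainty about the guess. What stands is that the text does not separate them.
- **That both arms share one chat group.** The mention of both groups belongs to the weekly phone call. The messenger group is opt-in, its stated subject is PD, and the trial runs at sites in two countries. A mixed group is plausible but not stated.
- **That the rule flatly contradicts intention-to-treat.** Section {11b} also excludes from the study participants with under 70% attendance, while {20c} makes attendance a criterion for the per-protocol set only. Exclusion may therefore mean leaving the programme and not leaving the intention-to-treat set. This is fair, but it does not supply the missing 12-week outcome. Exclusions under {11b} and {11d} raise the same difficulty; here the trigger is also a belief that the stimulus itself can prompt.
- **That the rule creates a spurious benefit of 0.195 to 0.350 SD.** Those values are right for removing exactly the worst 10% or 20% of the active arm, but that assumes perfect correlation and one direction only.
- **That evidence of failed blinding is lost.** Each report goes to the leading researcher, {22} says all dropouts will be reported, and nothing says week-6 answers are discarded. Only the end-of-programme question might lose respondents.

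**Conclusion.** The concern holds in a limited form. The protocol fixes a post-randomisation exclusion triggered by belief, which may depend on arm and on perceived benefit. It sits badly with the promised intention-to-treat analysis because outcomes for those excluded are not planned to be collected. Imputation would have to assume that exclusion is unrelated to the unseen outcome, given arm and baseline.

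Size and sign cannot be determined from the documents. With 20% excluded from one arm and ρ between 0.3 and 0.5, the bias is roughly 0.1 to 0.2 SD in either direction, against a planned effect of 0.80. With equal exclusion by the same mechanism it is zero. The rates and correlations are assumptions. The conclusion about the rule does not depend on them.

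The week-6 question and the messenger group are aggravating risks and not established routes to exclusion.

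**What to change.** - **Procedure for unblinding {17b}:** replace exclusion from the study with three steps: record the report and its date, carry out the 12-week outcome assessment, and keep the participant in the intention-to-treat set. Add a sensitivity analysis that omits participants who reported knowing their group, read as a non-randomised comparison.
- **Physical exercise program:** state that the allocation guess and confidence rating do not trigger exclusion.
- **Plans to promote participant retention {18b}:** make the messenger channel broadcast-only. Separate groups by arm could themselves hint at allocation.

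Whether the intervention continues after such a report is for the investigators to settle; the sections on exclusion, follow-up and analysis need to be reconciled on it.

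**Cost:** amended wording, submitted to the ethics committee as {25} requires, and the 12-week assessments of the few participants concerned. Some unblinded participants stay in the intention-to-treat set, which the sensitivity analysis addresses. A broadcast channel gives up the exchange between participants that the group was meant to offer. The change is needed during conduct, because outcomes not collected cannot be recovered at analysis.

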### Data collection and management

#### Plans for assessment and collection of outcomes {18a}

Both interventions (AMPS and exercise) will be carried out within the facilities of the Catholic University of Maule, located at [name], in the city of Talca, in parallel with Human Movement Research Laboratory of the São Paulo State University, Brazil. Evaluations will be conducted in a room with temperature maintained between 22 and 24 °C and relative humidity between 40 and 60% at the same time of day (2:00 p.m. to 6:00 p.m.) to minimize the influences of circadian variations. The methodological procedures for obtaining each outcome are detailed below:

##### Quality of life

Quality of life will be assessed by the Parkinson’s Disease Questionnaire 39 (PDQ-39), which is a questionnaire developed specifically for people with PD and consists of 39 items, and assesses 8 dimensions of daily life, including relationships, social situations, and communication [29]. It is validated for people with PD, has an acceptable internal consistency (α = 0.51 to 0.96), and proved to be reproducible (0.86 to 0.96) [30].

##### Heart rate variability

HRV is defined as the variation that occurs in the time interval between consecutive heartbeats and it has been proposed that its behavior depends on autonomic modulation, as well as its implications on cardiovascular mortality [31]. This time it will be done by continuous recording of RR intervals with 1000 Hz sampling frequency (Polar V800, Finland). R-R intervals will be recorded with a Polar V800 heart rate monitor (Polar, Oi, Finland); a sensor will be placed on the chest at the fifth intercostal space. Prior the beginning of data collection, volunteers will remain at rest for approximately 20 min for baseline heart rate and BP stabilization. Recording will occur under the following conditions: (1) resting in supine position for 15 min and (2) resting in orthostatic posture for 15 min. The volunteers will be instructed to maintain spontaneous breathing throughout the collection period in the supine and orthostatic postures. The participants’ respiratory rate will be recorded throughout the test. Heart rate variability will be analyzed through spectral analysis in an autoregressive model. The spectral components will be obtained at low frequency (LF, 0.04–0.15 Hz) and high frequency (HF, 0.15–0.4 Hz). The LF band is modulated by the sympathetic and parasympathetic autonomic nervous system (with sympathetic predominance), the HF band is associated with cardiac vagal control, and the LF/HF ratio is calculated to assess sympathovagal balance.

##### Peak oxygen uptake

All participants will undergo a cardiopulmonary exercise testing (CPET) studies in a global and non-invasive way the integral response of the organism to exercise, through a rational analysis of the respiratory, cardiovascular, hematopoietic, neuropsychological, and skeletal muscle systems [32] CPET will be performed with an ergometric bike (Ergoselect 5 M, Ergoline, Germany). An incremental ramp-type protocol will be used to determine the workload imposed on aerobic training and possible comorbidities that impede the performance of the proposed physical training protocol [33]. The outcomes VO2, carbon dioxide output (VCO_2_), ventilation (VE), and respiratory exchange ratio (RER) will be obtained on a breath-to-breath basis during the entire CPET using an expired gas measurement system (metalyzer 3b - Cortex Medical, Germany) duly calibrated before each test (this equipment is available for common use in our university). During CPET, electrocardiogram and heart rate (HR) will be continuously recorded in real-time via a 12-lead integrated ECG (Quark T12, Cosmed, Italy). Blood pressure and the ratings of perceived exertion using the Borg CR10 scale will be monitored throughout the test.

##### 24-h blood pressure

The electrocardiogram and blood pressure will be recorded for 24 h concomitantly through the 3 channel Cardio Map digital equipment, before and after the application of the protocol (Cardio Sistemas Comércio e Industria Ltda, Sao Paulo, SP, Brazil).

##### Sleep quality

Sleep quality will be assessed using an actigraph monitor (ActTrust, Condor Instruments Ltda) [34]. Sleep quality will be assessed by quantifying the sleep onset, sleep latency, sleep duration, sleep efficiency, and sleep disturbances. This device has been used in people with sleep disorders, obtaining very good results and demonstrating that it is a low-cost protocol, more durable assessment, and simple in its interpretation, also has good sensitivity and accuracy [35].

##### Timed up and go

It was designed to measure mobility in older people and has been recommended as a useful tool to quantify locomotor performance in people with PD [36]. It is also validated for adults with Parkinson’s with a sensitivity of 76%, a specificity of 66%, a positive predictive value of 39%, and a negative predictive value of 91% [34]. An instrumented TUG (iTUG) will be used to complement the results obtained from the TUG and to characterize the motor impairment resulting from the disease [37].

##### Tinetti scale

Evaluates the mobility of the elderly, the scale has two domains: gait and balance; its main objective is to detect those elderly people at risk of falling, it has a greater predictive value than the muscle test (Tinetti, 1986). It is also validated for adults with PD with a sensitivity of 76%, a specificity of 66%, a positive predictive value of 39%, and a negative predictive value of 91% [38].

##### 10-m walk test

It is a performance measure used to evaluate walking speed in meters per second over a short distance. It can be used to determine functional mobility, gait, and vestibular function [39]. The assessment measures the time in seconds it takes the patient to travel 10 m in a straight line. It will be applied in a corridor with a distance of more than 10 m and a flat surface. This test will be done 3 times conserving the best time that will be registered by 2 evaluators simultaneously.

#### Plans to promote participant retention and complete follow-up {18b}

A weekly phone call will be made to participants in both groups, asking about their health status and reinforcing the pre-session recommendations for physical exercise. Moreover, the participants who wish and agree, will be added to a telephone messenger group app with the objective of solving doubts and share information and experiences about PD.

#### Confidentiality {27}

The confidentiality of the identity will be safeguarded by the following measures:
Only the responsible researcher and his or her team will have access to the data collected during the evaluations.The interviews and data will be given a code for each participant, which will only be known by the researcher responsible for this study and will be carried out in an environment that encourages communication and anonymity chosen by the participant.

The data collected will be used only in academic research and research dissemination and will be available to researchers upon a reasonable request to the leading researcher.

#### Plans for collection, laboratory evaluation, and storage of biological specimens for genetic or molecular analysis in this trial/future use {33}

Not applicable, this trial does not have biological specimens.

### Statistical methods

#### Statistical methods for primary and secondary outcomes {20a}

The Shapiro-Wilk and Levene’s tests will be applied to check for data normality and the homogeneity of the variance, respectively. To check the interaction between the Groups (EX-G and AMPS-G) and time (baseline and post-intervention) a mixed ANOVA model with Bonferroni adjustment will be applied for the variables that meet the ANOVA assumptions. Otherwise, the data will be analyzed by the Wilcoxon (intragroup) and Mann-Whitney (intergroup) tests with a priori Bonferroni correction. For all tests, the significance level will be set at 5%.

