**Methods:**

A randomized, controlled clinical trial will be conducted. Older volunteers with PD will be randomly assigned to one of the two groups studied: (1) exercise or (2) AMPS + exercise. Both groups will undergo an exercise program of 24 sessions, for 12 weeks, performed twice a week. Before exercise sessions, the group AMPS + exercise will receive a session of active AMPS, while the group exercise will receive an AMPS sham intervention. Shapiro-Wilk’s and Levene’s tests will be used to check for data normality and homogeneity, respectively. In case parametric assumptions are fulfilled, per-protocol and intention-to-treat analyses will be performed using a mixed model analysis of variance to check for group*time interaction. Significance level will be set at 5%.

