#### Outcomes {12}

The results will be evaluated at 2 time points: (1) baseline (before starting the intervention program) and (2) after 12 weeks of intervention (after 48 h to 1 week from the last intervention). The primary outcomes will be (1) quality of life (PDQ-39), (2) heart rate variability (HRV) indices, and (3) VO2peak (cardiopulmonary exercise testing). Secondary outcomes include (1) 24-h blood pressure (3 channel Cardio Map digital equipment), (2) sleep quality (actigraph monitor), (3) VO2 at the anaerobic threshold (cardiopulmonary exercise testing), (4) dynamic balance (Tinetti Scale, TUG), and (5) gait velocity (10-m Walk Test).

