#### Sample size {14}

To determine the number of volunteers, the sample size was calculated using the GPower software version 3.1, for a 95% confidence level and 80% study power. The calculation was based on a pilot study (unpublished) that considered the LF/HF index of HRV, and systolic blood pressure. The largest suggested sample size was 19 volunteers per group to detect a decrease in systolic blood pressure with an effect size of 0.80. Therefore, considering possible dropouts, 25 participants will be enrolled for each group.

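### With two time points the planned group-by-time mixed ANOVA is a change-score t-test: valid, but less precise than a baseline-adjusted comparison, by an amount that depends on an unstated correlation

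*Protocol article*

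**What the plan says.** The section on statistical methods for primary and secondary outcomes {20a} names the model: "a mixed ANOVA model with Bonferroni adjustment will be applied for the variables that meet the ANOVA assumptions". The factors are group (EX-G, AMPS-G) and time (baseline, post-intervention). Variables that fail the assumptions go to Wilcoxon and Mann-Whitney tests. The Methods paragraph of the abstract confirms the target of the test: "using a mixed model analysis of variance to check for group*time interaction". Neither place names a baseline covariate.

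Outcomes {12} fixes the number of measurements: "The results will be evaluated at 2 time points". Under Implementation {16c}, the allocation envelopes stay closed until the baseline assessments are finished, so the baseline value cannot be affected by allocation.

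Sample size {14} was calculated "for a 95% confidence level and 80% study power". It gives this result: "The largest suggested sample size was 19 volunteers per group", in order "to detect a decrease in systolic blood pressure with an effect size of 0.80". Enrolment is then raised: "considering possible dropouts, 25 participants will be enrolled for each group". Section {20c} plans both per-protocol and intention-to-treat analyses, with multiple imputation.

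**The concern.** In a two-group, two-occasion design the interaction contrast is the difference between the groups in mean change. Analysing change fixes the coefficient of the baseline value at 1. When baseline and post values have equal spread, the data support a coefficient of about r. For r below 1, the change score therefore over-corrects a chance baseline difference and carries avoidable noise. Estimating the coefficient instead removes that noise.

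This matters because the trial is small, with 19 evaluable and 25 enrolled per group. The protocol names the less precise model, so an analysis plan could not adopt the better one without departing from the protocol text. What is at stake is the width of the confidence interval and the power, not the validity of the test.

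**Working it through.** **Inputs from the protocol.** Effect size 0.80, power 80%, 95% confidence, 19 per group (25 enrolled), all from {14}; two time points from {12}; 5% level from {20a}; 1:1 allocation from {8}. Not stated: the sidedness of the sample-size calculation, whether 0.80 is in SDs of the change or of the post value, and r. Assumed below: equal SD at both occasions and the same r in both groups.

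**1. The protocol's own figure.** Normal approximation, n per group = 2(z_α + z_β)²/d²:
- one-sided 5%: 2(1.645 + 0.842)²/0.64 = 19.3, so 20 (21 by the t distribution);
- two-sided 5%: 2(1.960 + 0.842)²/0.64 = 24.5, so 25 (26 by t).

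The stated 19 is close to the one-sided answer; one-sided power at 19 is 78% (t) to 79% (normal). The interaction F test is two-sided. Two-sided power is 67.0% at 19 and 79.1% at 25 by t, or 69.4% and 80.7% by the normal approximation. Going from 19 to 25 allows for 1 − 19/25 = 24% dropout.

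**2. Equivalence.** The interaction contrast is (post − baseline) in AMPS-G minus (post − baseline) in EX-G, so its F is the squared t from a two-sample test on change. A check on one simulated data set with 19 per group gave 9.292 for both.

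**3. Variance.** With SD σ at each occasion:
- change score: 2σ²(1 − r);
- baseline-adjusted: σ²(1 − r²);
- ratio: (1 − r²)/[2(1 − r)] = (1 + r)/2.

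The ratio is 0.65, 0.75, 0.85, 0.90 and 0.95 at r = 0.3, 0.5, 0.7, 0.8 and 0.9.

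**4. Power if 0.80 is in SDs of the change.** The effective size under adjustment is 0.80·√(2/(1+r)): 0.992, 0.924 and 0.868 at r = 0.3, 0.5 and 0.7. Noncentral t, two-sided 5%, one degree of freedom deducted for the covariate:

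| r (assumed) | 19/group: change | 19/group: adjusted | 25/group: change | 25/group: adjusted |
|---|---|---|---|---|
| 0.3 | 67.0% | 84.5% | 79.1% | 93.0% |
| 0.5 | 67.0% | 79.1% | 79.1% | 89.2% |
| 0.7 | 67.0% | 73.9% | 79.1% | 85.2% |
| 0.8 | 67.0% | 71.5% | 79.1% | 83.1% |
| 0.9 | 67.0% | 69.1% | 79.1% | 81.1% |

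**5. Power if 0.80 is in SDs of the post value.** The effective sizes are 0.80/√(2(1−r)) for change and 0.80/√(1−r²) under adjustment. At 19 per group:

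| r (assumed) | change | adjusted |
|---|---|---|
| 0.3 | 52.7% | 71.0% |
| 0.5 | 67.0% | 79.1% |
| 0.7 | 87.2% | 91.9% |
| 0.8 | 96.7% | 97.9% |

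Adjustment has the higher power in every row of both tables. The gain shrinks as r rises.

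**The case against.** The strongest reply is that nothing here is an error. A comparison of change is unbiased under 1:1 randomisation and answers the protocol's hypothesis of greater improvement. Covariate adjustment is often left to an analysis plan. The first part stands: this is an inefficiency, not an invalid test. The second part carries less weight, because the protocol does not leave the model open.

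A reader might also infer more than the document supports, in four ways:

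- **That the trial's true power is below 80%.** Sidedness and the SD behind 0.80 are unstated. One-sided, 19 per group gives about 78–79%. Two-sided with all 25 retained, power is 79.1% (t) or 80.7% (normal). On the post-value scale with r = 0.7, the planned test already has 87% at 19 per group.
- **That adjustment wins back most of a shortfall.** This depends on r. On the change scale at 19 per group, the share of the gap to 80% that is closed is 93% at r = 0.5, 53% at 0.7, 34% at 0.8 and 17% at 0.9.
- **That the Bonferroni adjustment is empty.** That would be so within a single 2×2 interaction, but {20a} does not say what it covers. If it splits 5% over the three primary outcomes (α = 0.0167, an illustration), it does act on the interaction p-value. Change-scale power at r = 0.5 would then go from 49.0% to 63.2% at 19 per group and from 63.7% to 78.0% at 25, still below 80% after adjustment.
- **That only the adjusted model pools simply after imputation.** The change-score difference is also a single coefficient and pools in the same way.

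**Conclusion.** The point holds as an efficiency improvement that should be made. The equivalence to a change-score t-test and the variance ratio (1+r)/2 are firm, given randomisation and equal spread at the two occasions. The size of the gain is not firm, because the document gives no r. At 19 per group on the change scale it is about 12 percentage points at r = 0.5 (67.0% to 79.1%), 7 at r = 0.7 and 2 at r = 0.9.

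All power figures rest on the 0.80 for systolic blood pressure, and Outcomes {12} lists 24-h blood pressure as secondary. Sample size {14} also mentions the LF/HF index but gives no effect size for it. Power for quality of life, HRV and VO2peak therefore cannot be computed from the document under either model. The benefit for those outcomes is known in direction but not in amount.

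**What to change.** In {20a} and the abstract, replace the mixed ANOVA for the between-group comparison with a linear model of the week-12 value on treatment group and the baseline value of the same outcome. Report the adjusted mean difference (AMPS-G minus EX-G) with its 95% CI, pooled over the planned multiple imputations by Rubin's rules in the intention-to-treat analysis. Change scores may still be shown descriptively.

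The replacement covers only the ANOVA branch, so the text should also say whether the rank tests remain for variables that fail the assumptions.

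The cost is a change of wording and one degree of freedom per model. No visit, measurement or participant is added.
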